### Intervention

The American Physical Therapy Association Guidelines [27] as well as the Australian Guidelines [63] both recommend the use of a multimodal intervention comprising of gentle exercise, advice to stay active and cervical mobilisation/manipulation. The usual care (UC) [40] will be given according to these guidelines to ensure that all patients receive evidence based care. No specific mobilisation/ manipulation technique have been shown to be superior to another [64, 28].

The UC will consist of mobilisation of the cervical and thoracic spine, exercises and advice to stay active. As most physiotherapists in South Africa have been Maitland trained, the patients will receive Maitland mobilisation [65] of the cervical and thoracic spine. Exercises will include postural correction, deep neck flexor training according to Falla et al. [66] and strengthening and mobilising exercises using yellow Theraband™ as described by [67]. All study participants will receive advice to stay active [27]. The number of treatments will range between two and a maximum of eight treatments and will be recorded. Patients who have not improved by the sixth treatment or patients who report any adverse events will be referred back to their general practitioners. Patients in the UC group will not receive any neural mobilisations.

The intervention group will receive the NM in addition to UC. The NM used in this study will be done as described by Butler [33], a gentle soft tissue mobilisation of the neural container/interface “along the tract” ([33] pp. 380) of the nerve – directly where the nerve is palpable and indirectly where it lies deeper. The treatment will concentrate on areas where the nerve is mechano-sensitive to palpation and will be done from the hand or elbow (depending on patient’s area of pain) and followed up along the arm, first rib, scalene and into the neck. Mobilisation will first be done in a position where the nerve is relaxed, not provoking any of the patient’s symptoms. Palpation may only provoke minimal symptoms and should disappear as soon as it is stopped. The basic principles of neural mobilisations will be used to progress treatment; that is to commence treatment in the acute phase with the nerve in a neutral, non-tension position and to progress into a more tensioned position as pain and irritability improves [33, 68].

### Statistical considerations

Primarily this study sets out to assess whether, six weeks after onset of treatment the NPRS score in the intervention group is reduced compared to the UC group. The sample size calculation is reported for the NPRS, which require the largest sample size.

### Data analysis

The data summary will employ descriptive statistics, means, standard deviations and 95% confidence intervals and will be reported by study group (intervention & standard care) for the NPRS, PSFS and EQ-5D. Catastrophising (yes & no) and neuropathic pain (yes & no) will be summarised using frequencies, percentages, cross tables and 95% confidence intervals.

Two treatment groups will be compared with respect to the change from baseline at six weeks in the NPRS, PSFS and EQ-5D scores using an analysis of covariance (ANCOVA) with baseline scores, catastrophising (yes & no) and neuropathic pain (yes & no) as covariates. For the total assessment period of 12 months the interaction between visits and treatment will be assessed with respect to NPRS, PSFS and EQ-5D scores in a linear mixed model analysis. Testing will be done at the 0.05 level of significance. For all data description and analyses an intention-to-treat analysis will be performed.

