### Aims of study

The aims of the study are firstly to establish the effect of NM on the pain, function and quality of life of patients with acute and sub-acute cervico-brachial pain. Secondly it aims to establish if high catastrophising scores and neuropathic pain have an influence on treatment outcomes.

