EuroQuol Instrument (EQ-5D) is a quality of life measurement and will be used to rate the quality of life of study participants. It has two sections: the first part consists of five sections namely mobility, self-care, usual activities, pain/discomfort and anxiety/depression. Each section is rated by three descriptions from “I have no problem” to “I am unable”. The second section of the questionnaire has a 20 cm Visual Analogue Scale with “best imaginable health state” at the one end and “worst imaginable health state” at the other end. The validity was established by measuring it against the SF-12 and positive correlations were found (r = 0.41). It has excellent reliability (ICC 0.82) [49]. Peolsson et al. [50] measured quality of life using the EQ5D in patients with cervical radiculopathy and whiplash associated disorder and found health related quality of life worse in these populations compared to a healthy group.

Patients will be asked to complete the Global Rating of Change Scale (GROC) six weeks after treatment has commenced. This scale measures the patient’s impression of improvement after an intervention. According to a review there are eight different scales [51]. In this study an 11 point Likert scale will be used with −5 representing very much worse, 0 is unchanged and +5 is fully recovered [51]. The test-retest reliability coefficient is good (ICC of 0.9). The scale correlates significantly with changes on the Roland Morris, Oswestry, Pain Rating Scale and the EQ-5D. According to Kamper et al. the Minimal Clinically Important Change of the GROC is two points on an 11 point scale [51]. Patients with a score of +3 or more will be considered “responders” and those with a lower score as “non-responders”.

Two questionnaires will be used to establish which patients have neuropathic pain and which patients are catastrophisers. These questionnaires will be repeated at six months and 12 months to measure if any change has taken place from initial assessment to one year follow up.

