The Neuropathic Pain Diagnostic questionnaire (DN4) consists of two sections namely an interview and examination. The interview has two questions, the first about the characteristics of the pain (e.g. burning) and the second about associated symptoms (such as pins and needles) to which the answer is either yes or no. In the examination, tests for hypoesthesia to touch and prick in the painful area as well as whether or not brushing aggravates the pain, are done. Each positive scores a point with a total score of 10. A patient with a score of 4/10 or more can be diagnosed with neuropathic pain [40]. The sensitivity of the test at the cutoff of four is 82.9 and the specificity is 89.9. The inter-rater reliability has Kappa values of between 0.70 and 0.96 [40]. This test have been used successfully in a South African population that are not all English first language speakers [52]. The questionnaire is recommended for use in the South African Guidelines for management of neuropathic pain [53].

The Pain Catastrophising Scale (PCS) is a questionnaire that establishes the levels of catastrophising present in patients. The questionnaire has three components: magnification, rumination and helplessness. Participants are asked to reflect on past painful experiences and to indicate the degree to which they experienced each of 13 thoughts or feelings when experiencing pain. It is scored on a 5-point scale from 0 “not at all” to 4 “all the time” with a maximum score of 52. A score above 24 classifies the patient as a catastrophiser [23]. The internal consistency of the three subscales are Crohnbach’s α of Rumination α = 0.85, Magnification α = 0.75 and Helplessness α = 0.85 [54]. The reliability as tested by Osman et al. [54] could correctly identify 77.1% of the cases. Osman et al. [54] also confirm the findings of Sullivan et al. [23] that the three dimensions represent a single construct.

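### The six-week ANCOVA enters catastrophising only as a yes/no class although the full 0–52 baseline score is collected, which discards graded prognostic information

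*Protocol article*

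**What the plan says.** The six-week comparison of change in the pain scale (NPRS), function (PSFS) and quality of life (EQ-5D) is made "using an analysis of covariance (ANCOVA) with baseline scores, catastrophising (yes & no) and neuropathic pain (yes & no) as covariates" (Data analysis). The yes/no form is therefore a stated choice and not a detail left open.

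Outcome measures describes the underlying scores. For the PCS, with 13 items: "It is scored on a 5-point scale from 0 “not at all” to 4 “all the time” with a maximum score of 52", and "A score above 24 classifies the patient as a catastrophiser". For the neuropathic pain questionnaire (DN4): "Each positive scores a point with a total score of 10", and "A patient with a score of 4/10 or more can be diagnosed with neuropathic pain". The same section gives the purpose of the two instruments: "Two questionnaires will be used to establish which patients have neuropathic pain and which patients are catastrophisers".

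The second aim reads: "Secondly it aims to establish if high catastrophising scores and neuropathic pain have an influence on treatment outcomes" (Aims of study). The article describes no analysis of either full score, and no power statement for this aim.

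**The concern.** With the split, a patient scoring 25 on the PCS counts the same as one scoring 52, and a patient scoring 24 the same as one scoring 0. The Background presents catastrophising as a predictor of poor outcome and mentions no threshold at which risk jumps.

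The second aim can be read as asking whether catastrophising predicts outcome. On that reading, the covariate term in the six-week ANCOVA is the model-based result that bears on it, since the 12-month mixed model names only the interaction of visit and treatment. The sample size was set for the NPRS treatment contrast alone, so the second aim has no planned reserve. A null result for catastrophising could then reflect the split and not an absence of influence.

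**Working it through.** **The plan's own figure.** Inputs from Sample size: difference 2, SD 2.05 inflated by √2 (2.90, variance 8.405), 2:1 allocation, one-sided 0.05, 90% power, dropout up to 20%.

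- Control group: 8.405 × (1 + 1/2) × (1.645 + 1.282)² / 2² ≈ 27, so 54:27, or 81 patients.
- With 20% dropout: 54/0.80 = 67.5 and 27/0.80 = 33.75, rounded up to 68:34, total 102.

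This reproduces the stated size. It takes no credit for covariates.

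**Assumptions.** The protocol does not give the partial correlation r of the PCS with the six-week outcome, or the share p of patients above the cut. I take r from 0.1 to 0.5 and p from 20% to 50%, with a normal score and a linear relation. The test is taken as two-sided at 0.05, because Data analysis does not restate sidedness.

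**Information kept by the split.** The share of explained variance kept is φ(z_p)² / (p(1 − p)), where z_p cuts off the upper share p and φ is the normal density.

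- p = 20%: 0.280² / 0.16 = 0.49
- p = 30%: 0.348² / 0.21 = 0.58
- p = 50%: 0.399² / 0.25 = 0.64

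The correlation shrinks by the square root of these: 0.700, 0.759 and 0.798.

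**Power of the covariate's main-effect test.** n = 81, four predictors (treatment, baseline, two covariates), 76 degrees of freedom, noncentrality √n · r / √(1 − r²). Example at r = 0.3:

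- As a score: 9 × 0.3 / √0.91 = 2.83, power 79.8%.
- As a split with p = 30%: r becomes 0.3 × 0.759 = 0.228, noncentrality 2.10, power 54.7%.

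| r | Score | Split, p = 20% | Split, p = 30% | Split, p = 50% | Loss (points) |
|---|---|---|---|---|---|
| 0.1 | 14.5% | 9.6% | 10.4% | 11.0% | 4–5 |
| 0.2 | 44.2% | 24.1% | 27.6% | 30.1% | 14–20 |
| 0.3 | 79.8% | 47.9% | 54.7% | 59.1% | 21–32 |
| 0.4 | 97.2% | 73.6% | 80.8% | 84.9% | 12–24 |
| 0.5 | 99.9% | 91.3% | 95.4% | 97.2% | 3–9 |

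A simulation of the full ANCOVA, with the two covariates correlated at 0.3, gave losses of 8–14 points at r = 0.2 and 12–23 points at r = 0.3.

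**If the relation is a step at the cut-off.** In the same simulation at r = 0.3 the yes/no form had 85–87% power, against 52–63% for the continuous score.

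**Primary treatment comparison.** 54:27, difference 2, SD 2.90 × √(1 − R²), one-sided 0.05, noncentral t. Unadjusted power is 89.6%.

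- One covariate at r = 0.3: 91.9% as a score, 90.7–91.0% as a split.
- Two independent covariates at r = 0.3, p = 20–30%: 94.1% against 91.8–92.2%.

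The gain is about 1–2 points here, and about 3 if both covariates have r = 0.4.

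**The case against.** The yes/no form answers the second aim nearly as worded. That aim speaks of high scores and of neuropathic pain, and the questionnaires are introduced as a means of classifying patients. The cut-offs are fixed in advance and cited, so there is no data-driven choice of cut-point. A continuous covariate estimates a slope per point, which is a different quantity. The protocol also never says that the covariate coefficients will be tested for the second aim, and it attaches no power claim to that aim. Baseline NPRS is already in the model and may carry some of the same prognostic information.

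Much of this stands. The sections agree with one another, so nothing is contradictory. For the DN4 the objection largely succeeds: a score of 4 or more is a diagnostic threshold with stated sensitivity and specificity, and the article does not present the 0–10 count as a graded measure of prognosis. A reader might infer that both splits are equally at fault; the documents do not support that.

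For the PCS the objection does not succeed. Fixing a cut-off in advance guards against picking it from the data, but does not restore the information lost within each class. A continuous score fixed in advance has the same protection.

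**Conclusion.** The point holds for the PCS, as an inexpensive improvement and not as an error that invalidates a result. Under a roughly normal score and a roughly linear relation, the split keeps about 49–64% of the explained variance. The power of a main-effect test for the second aim, in its prognostic reading, then falls by about 3–32 points over correlations of 0.1–0.5, with 20–50% of patients above the cut and 81 completers.

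Three stronger readings are not supported:

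- A reader might infer a flat loss of 20–30 points. That holds only near r = 0.3, close to the peak of the loss. The documents give neither the correlation nor the share above the cut, and the direction reverses if risk steps at the cut-off.
- A reader might infer that the primary comparison is underpowered or biased. Randomisation keeps it unbiased, the effect on its power is about 1–3 points, and the 90% power and total of 102 assume no covariate adjustment.
- A reader might infer that a null covariate result would be uninformative. Whether it would be depends on the unstated correlation; at r = 0.5 the split still has more than 90% power.

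**What to change.** In Data analysis, replace the yes/no catastrophising covariate with the baseline PCS total score (0–52) as a continuous covariate. Check linearity with a residual plot or a quadratic term. Keep the yes/no class for the frequency and cross tables already planned, and as a sensitivity analysis, which also covers a step at the cut-off. Neuropathic pain may stay as the DN4 diagnostic class; entering the continuous DN4 is optional.

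The cost is one sentence, with no new data, visits or patients. The downside is an assumed linear relation, and a coefficient per point (or per 10 points) in place of a difference between classes.

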**Discussion:**

In clinical practice neural mobilisations is commonly used for cervico-brachial pain. Although study outcomes seem promising, most studies have small participant numbers. Targeting the neural structures as part of the management plan for a subgroup of patients with nerve mechano-sensitivity seems feasible. Patients with neuropathic pain and psychosocial risk factors such as catastrophising, respond poorly to treatment. Although a recent study found these patients less likely to respond to neural mobilisation, the current study will be able to assess whether neural mobilisation has any added benefit compared to usual care. The study will contribute to the knowledge base of treatment of patients with cervico-brachial pain. The findings of the study will be published in an appropriate journal.

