Psychosocial factors have also been shown to play an important role in treatment outcomes [18–21]. Pool et al. [19] examined the influence of different psychosocial factors on treatment outcome and found fear of movement to be significantly correlated with poor outcomes in the short and long term. In a study by Karels et al. catastrophising was significantly linked to persistent symptoms of neck pain over a six-month period [22]. Catastrophising is a cognitive process that includes elements of magnification, helplessness, pessimism and is a consistently important predictor of poor pain-related outcomes [23]. Verhagen et al. [20] explored the influence of various factors on treatment outcome in neck pain and found pain severity and catastrophising to be the most important determinants for poor recovery. In a study to examine factors influencing return to work in patients with neck/arm/shoulder pain, the authors also concluded that psychosocial factors should be taken into account when interventions are planned [18]. Similar to these findings Thompson et al. [24] found catastrophising and poor self-efficacy to be associated with higher pain and disability. Other factors that have been shown to influence treatment outcomes are pain intensity at baseline, increased age and the presence of low back pain [25, 26].

Most clinical guidelines do not differentiate between treatment for neck pain and neck and arm pain such as cervico-brachial pain [27]. The American Physical Therapy Association recommends mobilisation/ manipulation of the neck and thoracic spine, exercises and education in the management of neck pain [27]. The findings of a recent Cochrane review confirm the above recommendations [28]. The American guidelines [27] also recommend that neural mobilisation should be considered for patients with neck and arm pain (level B evidence).

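### The second aim does not say whether it means prognosis or effect modification; the six-week ANCOVA answers only prognosis, while the abstract implies effect modification

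*Protocol article*

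**What the plan says.** Under Aims of study, the protocol article gives the second aim: "Secondly it aims to establish if high catastrophising scores and neuropathic pain have an influence on treatment outcomes". The wording mentions neither study arm.

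The Discussion part of the abstract notes that patients with neuropathic pain and psychosocial risk factors respond poorly to treatment, and that a recent study found a weaker response to neural mobilisation in them. It then says that "the current study will be able to assess whether neural mobilisation has any added benefit compared to usual care". The main Discussion section cites a review that asks for research into which subgroups respond to which interventions.

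Under Data analysis, the arms are compared on six-week change in NPRS, PSFS and EQ-5D "using an analysis of covariance (ANCOVA) with baseline scores, catastrophising (yes & no) and neuropathic pain (yes & no) as covariates". For the 12 months, "the interaction between visits and treatment will be assessed with respect to NPRS, PSFS and EQ-5D scores in a linear mixed model analysis". Otherwise the two factors "will be summarised using frequencies, percentages, cross tables and 95% confidence intervals". No factor-by-treatment term or subgroup contrast appears.

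Outcome measures gives the cut-offs: "A score above 24 classifies the patient as a catastrophiser" (maximum 52) and "A patient with a score of 4/10 or more can be diagnosed with neuropathic pain".

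**The concern.** Two different questions fit the second aim.

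- **Prognosis:** do patients with the factor have worse outcomes, whichever treatment they receive?
- **Effect modification:** is the difference between neural mobilisation plus usual care and usual care alone smaller (or larger) in patients with the factor?

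The aim does not choose between them. The stated model serves the first, and the abstract leans towards the second. If this is left open, a prognostic coefficient may be taken as evidence on who benefits from neural mobilisation. Alternatively, interaction terms may be added after the data are seen, when they carry less weight.

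**Working it through.** **1. What the stated model estimates.** Write Y for six-week change, T for treatment, B for the baseline score, C for catastrophising and P for neuropathic pain (both 0/1). The planned model is

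Y = a + b·T + c·B + d·C + e·P + error.

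The treatment effect is b for every patient, whatever C and P are. The coefficients d and e are adjusted differences by factor status, common to both arms. Effect modification needs f·T·C and g·T·P, which are not in the model. The visit-by-treatment term in the mixed model concerns time, not these factors.

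**2. The plan's own sample size.** Inputs from the Sample size section: difference 2, SD 2.05 × √2 = 2.899, 2:1 allocation, one-sided 0.05, 90% power, dropout 15-20%.

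Control n = (1.645 + 1.282)² × 2.899² × (1 + 1/2) / 2² ≈ 27, so 27 + 54 = 81 in total. At 20% dropout, 27/0.8 = 33.75, rounded up to 34, with 68 in the intervention arm. This reproduces 68:34 = 102. The figure is sized for the overall treatment difference only.

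**3. Precision of an interaction.** With 54:27 completers and a proportion p of patients having the factor, balanced across arms,

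SE = SD × √[(1/54 + 1/27) / (p(1 − p))] = SD × 0.2357 / √(p(1 − p)).

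The documents give no p, so 0.2 to 0.5 is assumed. Two SDs bracket the answer:

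- 2.899 is the protocol's change-score SD, with no credit for baseline adjustment.
- 2.05 is the ANCOVA residual SD implied by the same planning. The √2 inflation corresponds to zero correlation between baseline and follow-up, and under that assumption adjusting for baseline leaves a residual SD of 2.05.

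Power for a 2-point interaction, two-sided 0.05, is Φ(2/SE − 1.96). The last column uses a t reference with 81 − 7 = 74 degrees of freedom.

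| SD | p | SE | 95% half-width (1.96 × SE) | Power, normal | Power, t |
|---|---|---|---|---|---|
| 2.05 | 0.5 | 0.97 | 1.89 | 0.544 | 0.533 |
| 2.05 | 0.3 | 1.05 | 2.07 | 0.475 | 0.465 |
| 2.05 | 0.2 | 1.21 | 2.37 | 0.380 | 0.372 |
| 2.899 | 0.5 | 1.37 | 2.68 | 0.310 | 0.303 |
| 2.899 | 0.3 | 1.49 | 2.92 | 0.268 | 0.262 |
| 2.899 | 0.2 | 1.71 | 3.35 | 0.215 | 0.211 |

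A simulation with both interactions in the model (SD 2.899, all 102 patients) gave power of 0.36 at p = 0.5 and 0.29 at p = 0.3. The formula gives 0.375 and 0.325 there, so the table is slightly favourable.

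**4. The prognostic reading.** With 81 completers and SD 2.899, SE = 2.899 / √(81·p(1 − p)), which is 0.644, 0.703 and 0.805 for p = 0.5, 0.3 and 0.2. Two-sided power for a 2-point difference by factor status is 0.87, 0.81 and 0.70. The planned main effects therefore answer this reading reasonably well.

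**5. Cost of the yes/no coding.** For a normally distributed predictor, a cut that classes a proportion p as positive keeps φ(z)²/(p(1 − p)) of its explained variance: 0.58 at p = 0.3 and 0.64 at p = 0.5. If a factor explained 10% of outcome variance (assumed) and about 60% of that were kept, the treatment SE would grow by √(0.94/0.90) = 1.022, or about 2%.

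**The case against.** A reader might infer that the second aim cannot be answered at all. The documents do not support that. The aim speaks of influence on outcomes, and the Background uses nearly the same words for prognosis: one cited study "examined the influence of different psychosocial factors on treatment outcome and found fear of movement to be significantly correlated with poor outcomes". On that reading the coefficients of the planned covariates are the answer. This objection stands and sets the limit of the point.

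The abstract sentence can also be defended. It does not say that the added benefit will be assessed in these patients specifically, and overall added benefit is the first aim, which the ANCOVA addresses. That is fair as far as it goes. But the sentence is set against a reported weaker response in this very group, and the main Discussion stresses subgroups, so the treatment-specific reading is a natural one.

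A fuller protocol or analysis plan may contain interaction terms, so one cannot say that they will never be estimated. What remains is that the article writes out its model, and that model does not match the question its abstract raises.

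It is also tempting to call the dichotomised scores an error. They are not: the aim concerns high scores and a diagnosis, and the cut-offs are sourced. The loss to the primary comparison is small, and the 58-64% figure assumes normality, which suits a ten-item count such as the DN4 only loosely.

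Finally, the trial is too small to settle effect modification. That is true, and it is a reason to label the analysis exploratory rather than to leave the question unstated.

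**Conclusion.** The point holds as a mismatch between the aim, the abstract and the model. The stated ANCOVA answers whether the two factors are prognostic. It has no parameter for whether they change the effect of neural mobilisation. If interaction terms are added, power for a 2-point interaction is about 37-54% at a residual SD of 2.05 and about 21-31% at SD 2.90, with 95% half-widths of roughly 1.9 to 3.3 points. A 2-point interaction is as large as the whole treatment difference that the trial is designed to detect, so the result can only be exploratory. These figures assume 54:27 completers, a factor prevalence of 20-50% balanced across arms, and a two-sided 5% level. The primary treatment comparison remains valid.

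**What to change.** 1. In Aims of study, state whether the second aim concerns prognosis, effect modification or both.
2. In Data analysis, add a prespecified secondary analysis: the six-week ANCOVA with treatment-by-catastrophising and treatment-by-neuropathic-pain terms, preferably based on the continuous baseline PCS and DN4 scores. Report each interaction, and the treatment difference by factor status, with 95% intervals. Label the analysis exploratory because 102 patients were planned for the overall effect only.
3. State that the main-effect coefficients are prognostic and do not show who benefits from neural mobilisation.
4. Align the sentence in the abstract's Discussion with the question chosen.

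Optional: enter continuous PCS and DN4 scores in the primary ANCOVA for a small gain in precision, and keep the cut-offs for description.

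The cost is a little more analysis on baseline data already collected, and wide intervals that must be described as such.

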**Screening and allocation of patients.**

To be included in the study patients must be over the age of 18, with cervico-brachial pain as defined by Hall and Elvey [8]. This includes at least five of the following characteristics; antalgic posture, active movement dysfunction, passive movement dysfunction which correlate with the active movement dysfunction, adverse responses to neurodynamic tests which must relate specifically and anatomically to the active and passive movement dysfunction, and mechanical allodynia in response to palpation of specific nerve trunks. Lastly evidence from the physical examination of a local cause of the neurogenic pain must be present [8]. The upper limb neurodynamic test 1 (ULNDT1) will be considered positive if the patient’s pain is reproduced or partially reproduced by the test and changed by structural differentiation [41]. Patients with pain from recent onset (one day) up to 12 weeks, recurrent or first incident will be considered for inclusion. Patients with bilateral arm pain will also be considered for inclusion if they comply with the other inclusion criteria. Pain due to injury and the duration of pain will be recorded in the demographics questionnaire that patients will complete.

Patients who do not have a positive neurodynamic test will not be included in the study. Patients will be excluded from the study if they have had previous surgery or recent fractures of the cervical spine, serious neurological signs such as signs of spinal cord pressure or involvement of more than two nerve roots, conditions with long tract signs and those caused by other pathological diseases such as rheumatoid arthritis, neurological diseases, stroke, cerebral palsy, carcinoma or other red flags.

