### Sample size

Primarily this study sets out to assess whether, 6 weeks after onset of treatment the Numerical Pain Rating Scale NPRS score in the intervention group is reduced compared to the UC group. A blocked 2:1 ratio randomisation for intervention to usual care will be done using a computer generated random number list. A sample size of 68:34 i.e. a total sample of 102 patients will have 90% power to detect a clinically relevant increase of 2 for the change from baseline at six weeks in the NPRS score. A standard deviation of 2.05 was assumed as derived from the effect size reported by Bolton and Wilkinson [42]. The standard deviation was furthermore inflated by √2 since change from baseline is of interest. A dropout rate of 15 – 20% was assumed. One-sided testing will be done at the 0.05 level of significance. (nQuery advisor 7).

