### Initial assessment

Patients presenting at participating physiotherapy practices with neck and arm pain will be screened for inclusion into the study. Suitable candidates will receive a full musculoskeletal examination to confirm that they comply with the criteria for cervico-brachial pain as described above [8]. They will then complete the questionnaires as discussed.

Physical examination will include the ULNDT1. The test will be done as described above [33]. The range of ULNDT1 will be measured using a standard goniometer to measure the range of elbow extension [57]. The examination section of the DN4, that is; testing for hypoesthesia to touch, and prick and pain caused by brushing will be done at baseline, six months and 12 months. Neural conduction tests of sensation, muscle power and reflexes will be done according to Petty & Moore [58] at six and 12 months. They will also be asked to complete a demographic questionnaire on age, gender, duration of symptoms, previous neck pain, injury or insidious onset, education, occupation, sport, presence of headache or dizziness and indicate the area of pain on a body chart.

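### Pre-specifying age, which the protocol names as influencing outcome and already collects, as a covariate would be an optional, low-cost gain in precision; leaving it out is not an error

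*Protocol article*

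**What the plan says.** The primary question, in Statistical considerations, is whether "six weeks after onset of treatment the NPRS score in the intervention group is reduced compared to the UC group". Data analysis answers it with an analysis of covariance of the change from baseline at six weeks, "with baseline scores, catastrophising (yes & no) and neuropathic pain (yes & no) as covariates". The same model serves the function and quality-of-life scores. A linear mixed model covers the 12 months; the article names no covariates for it.

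The Background, after discussing catastrophising and other psychosocial factors, adds "pain intensity at baseline, increased age and the presence of low back pain" as further factors that influence treatment outcome. It gives no strength of association for any of them. Under Initial assessment, patients will "complete a demographic questionnaire on age, gender, duration of symptoms, previous neck pain" and several other items, so age will be on file for every patient. The Randomisation section describes 2:1 allocation in blocks of six and mentions no stratification by age.

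**The concern.** Data analysis gives a specific list of covariates. That list takes in baseline pain (for the pain score), catastrophising and neuropathic pain, each of which the Background links to outcome. Age stands in the same Background sentence as baseline pain, yet it is left out and no reason is given. Since no stratification by age is described, the analysis is the only described place where a chance difference in age between the arms could be dealt with.

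Two modest things are at stake: the width of the interval for the six-week difference, and protection if the arms happen to differ in age. Timing also matters. A covariate named in advance is credible, whereas one added after an imbalance has been seen looks driven by the data.

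**Working it through.** **Inputs from the protocol (Sample size):** target difference 2; 90% power; "One-sided testing will be done at the 0.05 level of significance"; SD 2.05, multiplied by √2 for change from baseline; allocation 2:1; total 102 (68:34); dropout 15-20%.

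**Assumption:** the share of residual variance that age explains, given the planned covariates, is not in the protocol. A range of R² = 2-10% is used, which corresponds to partial correlations √0.02 = 0.14 to √0.10 = 0.32. The true value for age could be lower, including zero.

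**1. Reproduce the planned sample size.** SD = 2.05 × √2 = 2.899. The normal-approximation formula for two means (one-sided 0.05, 90% power, 2:1) gives 27 + 54 = 81 evaluable. Then 81 / 0.80 = 101.25, rounded up to 102, or 34:68. This matches the protocol. The SD of 2.899 takes no credit for any covariate, so the stated power does not depend on age.

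**2. Find the SD that applies to the planned model.** Inflating by √2 amounts to a zero correlation ρ between baseline and six-week scores. A model that adjusts for baseline has residual SD 2.05 × √(1 − ρ²), which is at most 2.05, reached at ρ = 0. Any gain from age must be measured against this SD, not against 2.899.

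**3. Power without age, 54:27 evaluable.** The standard error is 2.05 × √(1/54 + 1/27) = 2.05 × 0.236 = 0.483. For a difference of 2, one-sided power from the noncentral t distribution is about 99.3% (two-sided about 98.3%). With ρ = 0.5 (assumed), the SD is 1.775 and one-sided power is about 99.9%. Almost no power is left to gain.

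**4. Effect of age on the standard error.** The standard error is multiplied by √(1 − R²):

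- R² = 2%: √0.98 = 0.990, a fall of 1.0%.
- R² = 10%: √0.90 = 0.949, a fall of 5.1%.

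The cost must be set against this. The planned model has five coefficients (intercept, treatment, three covariates), which leaves 81 − 5 = 76 degrees of freedom, or 75 with age. An uninformative covariate inflates the variance by roughly 1/75 = 1.3%. Net of that:

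- R² = 2%: variance factor 0.98 × 1.013 = 0.993, a fall of about 0.3% in the standard error.
- R² = 10%: 0.90 × 1.013 = 0.912, a fall of about 4.5%.

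**5. Chance imbalance.** The standardised age difference between arms has standard error √(1/68 + 1/34) = 0.210 as randomised and √(1/54 + 1/27) = 0.236 among evaluable patients. The chance that it exceeds 0.3 SD in either direction is about 15% and 20% respectively. Such an imbalance shifts an estimate not adjusted for age by 0.3 × √R² × 2.05:

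- R² = 2%: 0.3 × 0.141 × 2.05 = 0.09 points.
- R² = 10%: 0.3 × 0.316 × 2.05 = 0.19 points.

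Against the target of 2 points, that is about 4% to 10%.

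**The case against.** The strongest reply is that nothing in the protocol is misstated. The Background sentence is about prognosis and promises no adjustment. A randomised comparison with a pre-specified analysis of covariance is valid without age: it is unbiased over randomisations, it keeps its type I error, and the standard error already reflects chance imbalance. The chosen list also has a logic, since it holds the baseline score and the two factors of the study's second aim. All of this stands, and it is why the point is a suggestion only. It is also true that the size of the gain rests on an assumed R².

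The reply does not remove the suggestion. The protocol itself supplies the reason to adjust for age, the value is already collected, and naming it costs one line. An analysis plan that is not shown might add it; if so, nothing more is needed.

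Three stronger readings are tempting, and the documents do not support them.

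- A reader might infer that the trial loses power by omitting age, for instance by applying the assumed R² to the SD of 2.90. That is the unadjusted change-score SD. The planned model already adjusts for baseline, and on the protocol's inputs its power is already about 99%.
- A reader might infer that symptom duration belongs in the model on the same footing, because eligibility covers "Patients with pain from recent onset (one day) up to 12 weeks". The Background sentence that names age does not name duration, so its case rests on clinical reasoning from outside the document.
- A reader might infer that low back pain must be added as well, since the Background names it. It is not among the baseline items that the article lists, so including it would mean collecting a new variable. The argument from data already in hand does not reach it.

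**Conclusion.** The point holds as an optional improvement. The protocol names age as influencing outcome, collects it, and leaves it out of a fixed covariate list without giving a reason. The primary comparison remains valid and the sample size of 102 is unaffected.

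The benefit is a slightly narrower interval and cover against an unlucky age imbalance. Taken net of the lost degree of freedom, the fall in standard error runs from almost nothing to between 4% and 5%. These sizes rest on the assumed R² and on a residual SD of 2.05, the upper limit on the protocol's inputs; with a positive baseline correlation the shift in NPRS points would be smaller still. If age predicts nothing beyond the planned covariates, there is no gain and a variance cost of about 1%.

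**What to change.** In Data analysis, or in the analysis plan if one exists, add age as a continuous covariate to the six-week analysis of covariance and to the 12-month mixed model, and fix this before unblinding. If the sponsor prefers to leave age out, one sentence giving the reason would do.

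The cost is one line of text, one degree of freedom out of about 76, and about 1% of variance if age turns out not to be prognostic. No new data are needed and the sample size does not change. Symptom duration, also collected, may be added at the sponsor's discretion, but the protocol does not make the case for it.
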